### Unscheduled Visits

There are 2 reasons for an unscheduled visit.

1. If during the center-initiated telephone call to the patient the patient believes that they are having a relapse or if a patient should call the study center with complaint of a relapse, then the patient will be instructed to come in for an unscheduled visit within 7 days.

- Physical examination with vital signs
- Relapse reporting
- EDSS
- Adverse Events

2. If during the treatment phase a patient complains of symptoms related to medication side effects that the Treating Physician thinks requires a visit, the patient will come for an unscheduled visit.

# STATISTICAL METHODS

## Statistical evaluation

### Methods of statistical analysis

The methodology described in the protocol represents the methods foreseen at the time of writing, but advances in medical or statistical understanding may necessitate amendments to the approach, which will be documented in the statistical analysis plan. Full details of the methodology, including handling of missing or spurious data, will be described in the statistical analysis plan. No person privy to unblinded data will participate in discussions concerning changes in the statistical analysis plan.

All statistical hypothesis tests will be two-sided tests performed at the 5% significance level. All confidence intervals will be two-sided 95% confidence intervals unless stated otherwise.

### Evaluable subjects and analysis population

All efficacy and safety analyses will be performed on the set of all randomized patients who took at least 1 dose of study medication, i.e., the Full Analysis Set (FAS).

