**SW**iss **A**torvastatin and Interferon-**B**eta 1b Trial **I**n **M**ultiple **S**clerosis **Follow up-study**

**Short title “SWABIMS Follow up-study”**

**Study phase**  Phase IIb study

**Study design** Multi-center, randomized, rater-blinded, parallel-group-study in Switzerland

**Investigational product, dosage,** Atorvastatin 40 mg every day (oral) plus Interferon-beta

**route of administration** 1b 250g given subcutaneously (s.c.) every other day (e.o.d)

**Reference product, dosage,** Interferon-beta-1b 250g given

**route of administration** subcutaneously (s.c.) every other day (e.o.d)

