# Study Design

- Multi-center, rater-blinded, parallel-group, two arms, randomized study. Patients with relapsing-remitting forms of MS, **who have successfully finished the SWABIMS-Study**, respecting all inclusion/exclusion criteria, will be treated with the same medication they have received during the SWABIMS-Study for another 12 months directly after finishing the **SWABIMS-Study**.
- In the **SWABIMS-study**, 80 patients with relapsing-remitting MS were randomized to either an Interferon-beta-1b-monotherapy (subcutaneous every other day) **or** to a treatment with Interferon-beta-1b (subcutaneous every other day) plus Atorvastatin 40mg/d for 12 months after they were treated with Interferon-beta-1b (subcutaneous every other day) for 3 months.
- Enrolment of approx. 60 patients (one half in the Atorvastatin group) is planned.
- Patients providing written informed consent will be ***treated for 12 months***.

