## Selection of study population

### Inclusion criteria

- **Patients, who have successfully finished the SWABIMS-Study.**
- Patients with relapsing-remitting forms of multiple sclerosis (according to McDonald’s criteria)
- Patients must agree to avoid macrolids, including erythromycin and clarithromycin for the whole study duration
- Availability and willingness to continue study visits and procedures through month 12, even if discontinuation of study drug is necessary
- A woman of child-bearing potential must agree to avoid pregnancy with appropriate means while on study. Hormonal contraceptives used for more than 3 months are acceptable if therapy remains constant throughout the study
- Written informed consent
- Adequate bone marrow, renal, and hepatic function as defined in appendix.

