### Method of assigning patients to treatment groups

The treatment groups will be the same as in the SWABIMS-Study. Each patient continues the medication he/she received in the SWABIMS Study.

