## Acceptable ranges for laboratory findings

- Hemoglobin (Hb) ³9.0 g/dL
- White blood cell count (WBC) ³2,500 and £15,000/mm3
- Absolute neutrophil count (ANC) ³750/mm3
- Platelet count ³100,000/mm3
- Absolute lymphocyte count ³750/mm3
- Alanine aminotransferase (ALAT) £3 times the upper limit of normal
- Total bilirubin < 3.0 mg/dL
- Creatinine < 2.0 mg/dL at baseline
- CPK < 3 times upper limit of the normal range at baseline
- TSH < 6.75 mU/l

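### The follow-up study randomises nobody, yet it is labelled randomised and its only analysis set is all randomised patients; the groups compared are a subset selected after the SWABIMS randomisation

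*Protocol*

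**What the plan says.** The Synopsis describes the design as "Multi-center, randomized, rater-blinded, parallel-group-study in Switzerland", and section 7 (Study Design) repeats the randomised label. Section 11.1.2 defines the Full Analysis Set (FAS), the only analysis set in the Protocol: "All efficacy and safety analyses will be performed on the set of all randomized patients who took at least 1 dose of study medication".

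Allocation is described differently. Section 7.2.3 says: "The treatment groups will be the same as in the SWABIMS-Study. Each patient continues the medication he/she received in the SWABIMS Study". Section 7 says that patients "will be treated with the same medication they have received during the SWABIMS-Study for another 12 months". The only randomisation reported is that of 80 patients in SWABIMS (section 7). For the Follow-up study the same section says: "Enrolment of approx. 60 patients (one half in the Atorvastatin group) is planned".

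Entry is limited to "Patients, who have successfully finished the SWABIMS-Study" (section 7.1.1), where a successful finish is not defined. Patients must also meet the inclusion, exclusion and laboratory criteria (sections 7.1.1, 7.1.2 and 15.2), for example "CPK < 3 times upper limit of the normal range at baseline", and must give new consent (section 10.1).

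**The concern.** A Full Analysis Set built on randomised patients tells the reader that the groups were formed by chance and kept whole. Here neither the set nor the label describes what will be compared. Completion, renewed eligibility and the decision to continue all come after the SWABIMS randomisation, and all can be affected by the treatment received.

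The outcome most exposed is tolerability. Section 8.2.1 counts the drop-out rate due to adverse events as a safety variable, but patients who dropped out of SWABIMS have already gone when counting starts. New T2 lesions are exposed too, if the patients who do not continue differ in disease activity and do so differently in the two arms. A difference of that origin would be reported as a randomised FAS result.

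**Working it through.** **1. Is there a randomisation in this study?** Neither the schedule in section 9.1 nor the baseline procedures in section 10.1.1 contain such a step. Sections 7, 7.2.2 and 7.2.3 all continue the existing arms. There is none.

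**2. How large is the subset?** From section 7: 80 randomised in SWABIMS, about 60 planned here.
- Retained: 60/80 = 75%.
- Not carried over: 80 − 60 = 20, and 20/80 = 25%.

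The 60 is a planning figure, not an observed count, and the Protocol gives no calculation behind it.

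**3. Can the selection depend on treatment?**
- Section 7.2.2: Group 1 has had 12 months of atorvastatin by study entry; Group 2 has had none.
- Sections 7.1.2 and 15.2: myopathy, clinically significant liver disease, atorvastatin hypersensitivity, and ALAT and CPK outside the limits bar entry.
- Section 8.5.6: myopathy and rises in CK and transaminases are listed as expected with atorvastatin.
- Section 7.2.4: patients and treating physicians know the arm, so consent to continue is given with that knowledge.

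The criteria are the same in both arms, but in one arm they are applied after a year on the drug whose effects some of them screen for.

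**4. Does covariate adjustment repair it?** The primary model in section 11.1.4 adjusts for T2 and Gd-enhancing lesion counts, relapse rate and EDSS at baseline, among others. Sections 10.1 and 10.2 place the baseline visit at SWABIMS month 15. If the covariates are taken there, they follow 12 months of atorvastatin in Group 1. Adjustment may reduce a selection effect that acts through them. It does not restore the randomised comparison, and it may remove part of a true effect.

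**5. How large could the bias be?** The Protocol gives no event rate and no retention by arm, so everything here is assumed: 40 randomised and 30 retained per arm, and a true risk of new T2 lesions of p = 0.5 in both arms. With q the risk among the 10 leavers of an arm:

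retained risk = (40p − 10q)/30

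| Leavers' risk, atorvastatin arm | Leavers' risk, control arm | Retained risks | Odds ratio |
|---|---|---|---|
| 0.5 | 0.5 | 15/30 = 50% vs 15/30 = 50% | 1.00 |
| 0.7 | 0.5 | 13/30 = 43% vs 15/30 = 50% | (13/17)/(15/15) = 0.76 |
| 0.3 | 0.5 | 17/30 = 57% vs 15/30 = 50% | (17/13)/(15/15) = 1.31 |

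The second row corresponds to atorvastatin-arm retention of 65% in patients with new lesions and 85% in those without: 0.5 × 0.65 / (0.5 × 0.65 + 0.5 × 0.85) = 0.325/0.75 = 43%. Exact enumeration at 30 per arm gives these unadjusted false-positive rates:

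| Selection in the atorvastatin arm | Apparent risks | Fisher | Chi-squared |
|---|---|---|---|
| None | 50% vs 50% | 2.7% | 5.2% |
| 65% / 85% retained | 43% vs 50% | 4.8% | 8.3% |
| 55% / 95% retained | 37% vs 50% | 12.0% | 18.1% |

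Arm sizes stay at 30 and 30 throughout, so balanced numbers would not reveal the problem.

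**The case against.** The carry-over of arms is stated openly and repeatedly, and the arms do originate in a randomisation. What is missing is the caveat that the groups were selected afterwards. That is fair, and it is why the remedy is mostly wording. Full methodology is left to a statistical analysis plan that is not at hand. However, the Protocol itself fixes the analysis set and the design label, and a later plan cannot turn a continuation into a randomised comparison.

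A reader might infer three stronger things that the document does not support.

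- *That the analysis set is the 80 SWABIMS patients.* They are the only randomised patients described, so the words allow it, but the rest of the Protocol makes it strained. Section 7.1.3 uses the term randomised patient for someone kept on this study's visit schedule. Sections 10.1 and 10.2 start treatment at the new baseline after new consent. Sections 8.4 and 11.1.3 compare scans at study entry and Month 12, which only enrolled patients have.
- *That non-responders are screened out of the atorvastatin arm.* No entry criterion refers to relapses, lesions or EDSS worsening, and the undefined successful finish cannot be read that way without guessing. Patients may choose not to continue, but nothing shows that this differs by arm. The documented route is tolerability, and nothing in the Protocol links statin intolerance to new T2 lesions.
- *That the bias is as large as 43% against 57% (odds ratio 0.58).* That result needs leavers' risks of 0.7 in one arm and 0.3 in the other, that is, selection in opposite directions in both arms. With selection in the atorvastatin arm alone the same formula gives 43% against 50%.

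The illustrations also use crude risks, whereas the primary comparison is covariate-adjusted, so they should not be read as the bias of the primary analysis.

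**Conclusion.** The point holds as a defect of definition and labelling that has an inferential consequence. The analysis set and the design description both rest on a randomisation that this study does not perform, and about 25% of the randomised patients are expected to be absent from the groups compared. Selection bias is possible and randomisation no longer prevents it. The concern is strongest for tolerability and adverse-event drop-outs, where the entry criteria bear directly on atorvastatin effects, and weaker for new T2 lesions, where an arm-dependent link between leaving and lesion activity has to be assumed.

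Size and direction are unknown. The figure of 43% against 50% (odds ratio 0.76) shows what moderate one-arm selection could do on assumed inputs; it is not an estimate for this trial. At that level Fisher's test still rejects in under 5% of trials, and the 12.0% rate needs much stronger selection.

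**What to change.** 1. In section 11.1.2, define the FAS as patients enrolled in the Follow-up study who took at least one dose of study treatment in it, grouped by SWABIMS arm. State what counts as study treatment in each group, because section 7.2.7 uses the term investigational product for atorvastatin only, which Group 2 does not take.
2. In the Synopsis and section 7, describe the design as a continuation of the SWABIMS arms without new randomisation, and bring the wording of section 7.1.3 into line. Limit conclusions to patients who completed SWABIMS and continued.
3. Report the flow from 80 to about 60 by arm with reasons, and tabulate SWABIMS pre-randomisation characteristics of continuers and non-continuers by arm.
4. Optionally, add a sensitivity analysis weighting continuers by the inverse probability of continuing. With only about 20 non-continuers it would be imprecise and could be supportive at most.

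The cost is wording in a few sections, one flow summary and one table from SWABIMS data, and a more modest claim. No treatment rule or visit changes.

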### Study endpoints

**Primary Endpoint**

The primary efficacy endpoint is the proportion of patients in each treatment group with new T2 lesions after 12 months of treatment. The presence of new T2 lesions will be determined by comparing the results of the blind review of the MRI scans between study entry and Month 12.

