In an open-label, single-arm study in ***patients with relapsing-remitting multiple sclerosis*** on use of oral simvastatin (80 mg), the mean number and volume of gadolinium-enhancing lesions compared to pretreatment brain MRI scans declined by 44% and 41% respectively, while treatment was well tolerated (17). In a very small study lovastatin therapy showed beneficial effects on the expanded disability status scale (EDSS), relapse rate and Gd-enhancing lesions (25).

**Multiple sclerosis patients** respond variably to monotherapies, which could be explained by different subtypes of multiple sclerosis and multiple environmental and genetic factors. Oral statins decrease neuroinflammatory activity and clinical signs in experimental allergic encephalomyelitis and showed beneficial effect in smaller studies in multiple sclerosis patients. Therefore, statins may have favourable clinical effects in patients with relapsing-remitting disease as single therapy, or administrated as combination therapy with interferon beta. To determine the therapeutic effect of statins in multiple sclerosis, further investigations of statins as therapeutic agents for MS should be addressed in larger controlled clinical trials and longer observation periods.

In this study the effect of Atorvastatin as add-on therapy in patients with RR-MS, already treated with interferon-beta-1b vs. treatment with Interferon-beta-1b alone will be evaluated over another 12 months after finishing the SWABIMS Study as a Follow up study of the SWABIMS-Study. The treatment of each patient will be the same. Furthermore important safety and tolerability data will be generated.

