## Magnetic resonance imaging (MRI)

All patients will undergo MRI examination at the time of study entry and at month 12. The study scans should be performed within 14 days of the scheduled visit. If a patient receives a high dose of corticosteroids to treat an exacerbation, then the MRI scan will be postponed until 30 days after the treatment is completed. MRI scans are to be performed following standardized MRI guidelines (see detailed protocol) and will include pre and post contrast,T1 images and T2 images. The MRI scans will be analyzed centrally in a blinded fashion at the MRI core lab. MRI is used in this study as a parameter of activity. Recent studies have shown that the number of T2 positive areas and the number of new lesions on the T2-weighted images considered correlates with the activity detected by MRI with gadolinium, and shows a positive trend in the progression of the disease. Furthermore, new T2 lesions reflect disease activity over the whole interval of 3 months, whereas gadolinium-enhancing lesions reflect only the previous month. A highly concentrated contrast agent will be used for the T1 sequences, to evaluate disease activity of the last month by means of gadolinium-enhancing lesions. T1-weighted sequences of MRI scans will be performed with high concentrated gadobutrol. The contrast medium may occasionally cause nausea and vomiting, it may cause warmth and pain at the injection site. Allergic reactions occur very rarely (anaphylactic shock in 13 of 5 million applications, based on post-marketing surveillance) and in extremely rare instances can be potentially serious.

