### Statistical analyses

**Primary Endpoint**

The number and proportion of patients with new T2 lesions at month 12 will be summarised by treatment group. A Fisher’s Exact Test (or chi-squared test, if required) will be conducted to test for the unadjusted influence of treatment group.

The primary comparison between the groups will be performed using a logistic regression analysis. In addition to a term for treatment, the following terms will be included in the logistic regression model: number of T2 lesions at baseline, number of Gd-enhancing lesions at baseline, relapse rate at baseline, baseline EDSS score, time since diagnosis, sex. The results will be presented as odds ratios, and associated 95% confidence intervals and p-values.

The number of T2 lesions at Month 12 will also be analysed, using analysis of covariance (ANCOVA). In addition to a term for treatment the following covariates will be included in the model: number of T2 lesions at baseline, number of Gd-enhancing lesions at baseline, relapse rate at baseline, baseline EDSS score, time since diagnosis, sex.

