### MRI scan analysis

Two experienced observers will be in charge of lesion identification and counting. All scans from a given patient will be evaluated by the same observer. Doubtful cases will be assessed by the observers by consensual agreement. The readers were masked to clinical events or treatment.

A single enhancing lesion is defined as an area of enhancement seen on a given 3 mm axial image, which is referable neither to normally enhanced structures, nor to contrast migration within vessels. T2-weighted FSE/TSE images will be used as reference for analysis. A single T2 lesion is defined as an area of increased signal on a given 3 mm axial image, which should be seen on both T2- and proton density-weighted images and which is not referable to normally hyperintense structures. Lesions that changed during the study were categorized as new, enlarging, or recurrent. New T2 lesions are those which appear in areas where on the previous scan no abnormality was detected.

Lesion load will be assessed by trained technicians. The same technician will measure abnormalities on the scans from the same patients throughout the entire study. The image analysis will be performed using a semi-automated segmentation technique based on local thresholding.

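### The only T2 count analysis uses the total Month 12 lesion number, so the number of new T2 lesions per patient is never analysed

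*Protocol*

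**What the plan says.** Protocol section 11.1.3 defines the primary outcome: "The primary efficacy endpoint is the proportion of patients in each treatment group with new T2 lesions after 12 months of treatment". On its derivation it says "The presence of new T2 lesions will be determined by comparing the results of the blind review of the MRI scans", the two scans being study entry and Month 12. Section 11.1.4 tests it by logistic regression with six baseline terms, plus an unadjusted Fisher or chi-squared test. It then adds one count analysis: "The number of T2 lesions at Month 12 will also be analysed, using analysis of covariance (ANCOVA"; the covariates are the same six terms, including the baseline T2 number.

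Appendix section 15.1.6 puts two masked observers in charge of finding and counting lesions, and has changed lesions sorted into categories, one of which is new. It defines that category: "New T2 lesions are those which appear in areas where on the previous scan no abnormality was detected".

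The secondary endpoints (sections 6.2, 8.1.2 and 11.1.4) cover Gd-enhancing lesions, T2 volume, disability, relapses, atrophy and antibodies. The number of new T2 lesions is not among them. On size, section 7 says "Enrolment of approx. 60 patients (one half in the Atorvastatin group) is planned". No power, effect or lesion rate is given.

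**The concern.** The supportive count analysis should recover what the yes/no endpoint discards, namely how many new lesions each patient formed. It uses a different quantity. A Month 12 total adjusted for the baseline total is in effect new lesions minus lost lesions plus recount error. A patient with three new and three resolved lesions scores as unchanged. The model also assumes normal errors for what is likely a skewed outcome; the non-parametric fallback in 11.1.4 is written for the secondary endpoints, not for this analysis.

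The Protocol's own reasoning is on the new-lesion scale. Section 8.4 supports T2 as an activity marker because "the number of new lesions on the T2-weighted images considered correlates with the activity detected by MRI with gadolinium". Section 5 reports earlier statin evidence as a fall in mean lesion number: "the mean number and volume of gadolinium-enhancing lesions compared to pretreatment brain MRI scans declined by 44% and 41% respectively". With about 60 patients and no replacement of withdrawals, a supportive analysis that adds avoidable noise is a real loss.

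**Working it through.** The Protocol states no power figure, so there is none to reproduce.

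**Inputs from the Protocol.** 30 per arm (section 7); for the level, "All statistical hypothesis tests will be two-sided tests performed at the 5% significance level" (section 11.1.1).

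**Assumed inputs.** New-lesion counts are negative binomial with control mean m from 0.5 to 3 and shape k from 0.5 to 1. The mean reduction is 44%, borrowed from section 5, where it refers to Gd-enhancing lesions in an open-label, single-arm simvastatin study. Mean baseline T2 count is 30, 5% of lesions resolve, and recount error has SD 1. Comparisons are unadjusted, except that the ANCOVA uses the baseline T2 number.

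**1. What the planned ANCOVA measures.** Month 12 total = baseline + new − resolved + recount error. Given baseline, the variance is Var(new) + Var(resolved) + Var(error).
- Var(new) = m + m²/k.
- Added noise = 30 × 0.05 × 0.95 + 1² = 2.425.

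**2. What the noise costs (normal approximation, k = 1).**
- m = 2 v 1.12: variances 6 and 2.374, average 4.187; difference 0.88. On new lesions alone, SE = √(2 × 4.187/30) = 0.528, z = 1.67, power about 38%. With the noise, SE = √(2 × 6.612/30) = 0.664, z = 1.33, power about 26%.
- m = 0.5 v 0.28: variances 0.75 and 0.358, average 0.554; difference 0.22. New lesions alone: SE = 0.192, z = 1.14, power about 21%. With the noise: SE = √(2 × 2.979/30) = 0.446, z = 0.49, power about 8%.

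The noise matters most when new lesions are few.

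**3. Simulated power of the count analyses.** Three forms of the same 44% mean reduction were used: every rate scaled (proportional), half the patients with an 88% reduction (mixed), and 44% of patients fully suppressed (responder). Over the grid, a negative binomial test on new lesions has about 17% to 43% power against 8% to 33% for the total-T2 ANCOVA. It was higher in every scenario. When its critical value is raised to hold 5% size, the advantage shrinks and is close to nil at m = 3, k = 1 with a responder effect.

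**4. Against the yes/no test.** P(any new lesion) = 1 − (k/(k + m))^k. For m = 2, k = 1, the control value is 1 − 1/3 = 67%.
- Proportional: treated 1 − 1/2.12 = 53%, difference 14 points.
- Responder: treated 0.56 × 67% = 37%, difference 29 points (unrounded).

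| m = 2, k = 1 | Chi-squared, any v none | Negative binomial, new count | ANCOVA, total T2 |
|---|---|---|---|
| Proportional | 18% | 41% | 25% |
| Responder | 64% | 34% | 24% |

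Under a proportional effect the count gains about 5 to 27 points over the yes/no test across the grid. With the size held at 5%, the gain at m = 0.5 is only 2 to 3 points.

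**The case against.** A reader might infer that the primary endpoint itself should become the new-lesion count, because dichotomising throws away power. The documents do not support that. The gain needs treatment to scale every patient's lesion rate, which the Protocol nowhere assumes; section 5 says that patients vary in their response to single therapies. Under a responder effect with the same mean reduction, the yes/no test wins clearly. The gain is also small at low lesion rates, which are plausible because all patients are on interferon-beta-1b and have already completed the parent study. The endpoint is stated consistently and is easy to interpret.

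Other objections also carry weight. The 44% is not a controlled estimate for atorvastatin added to interferon. The power of the planned adjusted logistic model was not calculated. The total-T2 ANCOVA is not worthless: with m = 2, k = 1 and a rate ratio of 0.5 it has 37%, between 25% for the yes/no test and 53% for the negative binomial. One observer reads all of a patient's scans, which limits recount error. Section 11.1.3 speaks only of presence, so a stored per-patient new-lesion number is inferred from 15.1.6.

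These points defeat a change of primary endpoint. They do not defend the total count as the supportive outcome: a single observer does not stop resolving lesions from cancelling new ones. Nor is this a detail left to the SAP, since the Protocol itself fixes the analysis.

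**Conclusion.** The point holds for the supportive analysis only. The Protocol commits to a net-change measure where the count of new lesions is obtainable from the same reading and matches the primary endpoint. On the assumptions above, analysing new lesions gives about 17% to 43% power against 8% to 33%, with the advantage nearly vanishing in the least favourable size-adjusted case. Every figure depends on the assumed lesion rate, dispersion, effect pattern, resolution and recount error.

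Power stays low either way, so the change will not make a null result conclusive. It gives a better-targeted second look at the primary question. It is a recommended improvement, not an error that invalidates the plan, and no ground for replacing the primary endpoint.

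**What to change.** Keep the proportion of patients with new T2 lesions as the primary endpoint. In 11.1.4, replace the ANCOVA of the total T2 number, or precede it, with an analysis of the number of new T2 lesions per patient between study entry and Month 12. Use negative binomial regression, report the rate ratio with its 95% confidence interval, and add a permutation or rank-based p-value as a check on fit and small-sample size. State in 15.1.6 that the readers record this number for each patient.

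The cost is wording, settled before the readings are linked to treatment group, and export of one more variable from the MRI reading. No scan, visit, reader or patient is added. The downside is that a few very active patients can influence the rate ratio; the rank-based check and the retained proportion guard against over-reading it.
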